#### 4.5.2. Module II

**Hospitalization and Discharge (Hospital Admission Day, with follow-ups every 48 h)**

1. Structured assessment of patient and caregiver needs, along with patient and caregiver education, including communication with the patient and family to establish a treatment schedule and set an expected discharge date.

2. Review of the prehabilitation protocol from Visit 2.

3. Evaluation and identification of patient needs related to mobility, nutrition, pharmacotherapy, and psychological support.

4. Assessment of the support capabilities of family members or caregivers.

5. Communication with a family member or caregiver who will provide posthospital assistance.

6. Providing the patient and caregiver with an overview of the hospital stay schedule, postprocedure activities, and discharge plan.

7. The patient’s stay in the ward will adhere to the SAFER Patient Flow Bundle.

#### 4.5.3. Module III

**Postoperative Recovery (From the first day after the surgical procedure)**

Surgical Procedure and Hospitalization Assessment:Health Assessment: Regular monitoring of health parameters and treatment progress;Registration of the ICD-10 and ICD-9 procedure codes;Clavien–Dindo classification for complications;Evaluation of perioperative pharmacotherapy;Registration of anesthesia type;Monitoring of postanesthesia complications;Wound healing assessment via the VAS scale.Enhanced Recovery Protocol (early patient mobilization, bedside rehabilitation, gradual physical activation, nonstandard dietary management, additional rehabilitation support).Daily Red to Green assessment.Evaluation of family communication needs.The patient’s stay in the ward will adhere to the SAFER Patient Flow Bundle.

#### 4.5.4. Module IV

**Comprehensive Discharge Support System (30-day Post-Surgery Period)**

Transitional Care Program:Contact with primary care providers and community nurses;Scheduling of oncological consilium;Development of discharge and long-term care recommendations.Reinforcement of SAFER Patient Flow Bundle standards, with coordination between the social worker and a nurse to establish optimal conditions for early discharge and ensure an individualized transitional care program.Monitoring and Analysis of Prolonged Hospitalizations and Rehospitalizations:Analysis of the reasons for PH/RH;Review of treatments administered;Assessment of therapeutic outcomes achieved;Evaluation of the impact on the patient’s overall condition.

**Follow-up Visit (Day 30 ± 5 after surgery)**

A follow-up interview will be conducted at day 30 ± 5 after surgery to assess changes in general health status compared with Visit 1, document the postoperative course, and repeat applicable scales. The follow-up may be conducted by telephone or on site at the study center.

For an on-site follow-up visit, the histopathology results and treatment outcomes will be reviewed when applicable.Nutritional assessment will include anthropometric measurements (BMI and WHR), bioelectrical impedance analysis, and consultation with a clinical dietitian.Psychological assessment will be conducted using the HADS.Physical-function assessment will include handgrip strength, the six-minute walk test, FEV1, and the sit-to-stand test.A clinical pharmacist assessment will be performed.

The examination of participants will take place in accordance with the table below (Table 1).

## 5. Outcome Measures

The three primary outcomes are objectively defined clinical measures: prolonged index hospitalization, unplanned hospital readmission, and postoperative complications. Prolonged index hospitalization is defined as an index hospital stay lasting ≥ 14 calendar days from admission to discharge. Readmission is defined as an unplanned admission to the same or another hospital within 30 days after discharge from the index hospitalization. Postoperative complications are assessed for 30 days after the index surgical procedure.

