During hospitalization, adherence to enhanced recovery principles and standardized perioperative care is monitored continuously by the multidisciplinary team. After discharge, transitional care includes scheduled follow-up contacts, reinforcement of discharge recommendations, and monitoring for complications and rehospitalization.

Adherence is documented prospectively using the RESET digital platform, activity-monitoring wristband, follow-up assessments, and routine study documentation. Indicators include attendance at scheduled consultations, implementation of physical activity, nutritional, and medication-related recommendations, use of the application, and completion of planned follow-up activities. These process measures will be analyzed together with clinical outcomes to assess intervention fidelity, feasibility, and implementation.

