### 5.1. Primary Endpoints

Participants with prolonged index hospitalization.

The outcome will be reported as the number and percentage of participants whose index hospitalization lasts at least 14 calendar days. The number of days beyond day 14 and the number of consecutive clinically unjustified Red days at the end of hospitalization will also be recorded.

2.Participants with an unplanned hospital readmission within 30 days after index hospital discharge.

Readmissions will be identified using electronic health records, hospital information systems, and participant follow-up interviews. The outcome will be reported as the number and percentage of participants with at least one unplanned readmission within 30 days after discharge.

Prolonged hospitalization and readmission will be compared between the RESET and standard-care arms. Additional analyses will describe the duration and reasons for prolonged hospitalization, time to readmission, causes of readmission, associated treatment, impact on the participant’s condition, and related costs.

3.Participants with at least one postoperative complication within 30 days after surgery.

Postoperative complications will be identified and graded using the Clavien–Dindo classification. The outcome will be reported as the number and percentage of participants with at least one Clavien–Dindo grade I-V complication within 30 days after surgery. For participants with multiple complications, the highest grade observed during this period will additionally be recorded.

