## 6. Discussion

RESET evaluates an integrated perioperative pathway combining individualized prehabilitation, coordinated inpatient care, structured discharge planning, and transitional care. Existing evidence suggests that prehabilitation can improve functional capacity and selected postoperative outcomes, but effects vary across populations, intervention content, and implementation settings [1,4,6,7,8,9,10,11,12,13,14,15,16]. The present trial therefore tests the effectiveness of the integrated pathway rather than assuming that benefits of individual elements will translate directly to the complete RESET model.

The clinical rationale is particularly relevant to patients with cancer and older surgical patients, in whom limited physiological reserve, frailty, multimorbidity, nutritional deficits, and short preoperative windows may modify response to optimization. Prolonged hospitalization and readmission are also multifactorial outcomes that reflect perioperative morbidity, discharge preparation, access to follow-up, patient and caregiver support, and organizational factors [29,30,31]. RESET addresses these domains within one coordinated pathway spanning the preoperative, inpatient, and 30-day post-discharge periods.

The 9:1 allocation increases experience with delivery and implementation of RESET while preserving a randomized standard-care comparator, but the smaller control group necessarily reduces statistical efficiency compared with balanced allocation. The protocol’s generic reference calculations should therefore not be interpreted as guaranteeing 95% power for every endpoint-population hypothesis. The current manuscript reports conservative endpoint-specific design-sensitivity benchmarks under the planned allocation and the first Holm step; the SAP will document the full family-wise operating characteristics before database lock and before treatment effects are examined.

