## Figures and Tables

**Figure 1 mps-09-00134-f001:**
[figure not shown]
Flowchart of patient enrollment and participation.

**Table 1 mps-09-00134-t001:** Schedule of activities.

Procedure/Activity	Module I—Visit 1 21 ± 7 Days Before Surgery	Module I—Visit 2 Hospital Admission	Module II Hospitalization and Discharge	Module III Postoperative Recovery	Module IV 30-Day Post-Surgery Period	Final Visit 30-Day Post-Surgery Follow-Up
Informed consent	**X**					
Inclusion/Exclusion Form	**X**					
Demographics	**X**					
Medical history	**X**					**X**
Randomization	**X**					
RESET intervention	**X**	**X**	**X**	**X**	**X**	
Physical exam	**X**	**X**	**X**	**X**	**X**	**X**
Medical Laboratory Diagnostics	**X**	**X**	**X**	**X**		**X**
Nutritional assessment	**X**	**X**				**X**
Psychological evaluation	**X**	**X**				**X**
Physiotherapy assessment	**X**	**X**				**X**
Clinical pharmacist assessment	**X**	**X**				**X**
Addiction-related re-education (if applicable)	**X**					
Installation of a mobile app + wristband	**X**					
Activity Level Evaluation		**X**				**X**
Medical Scales Assessment	**X**	**X**	**X**	**X**	**X**	**X**
Treatment plan discussion		**X**				
Participant Satisfaction Survey		**X**				**X**
SAFER Bundle		**X**	**X**	**X**	**X**	
Red to Green		**X**	**X**	**X**	**X**	
Early Mobilization Program				**X**		
Transitional Care Program					**X**	
Complete Visit Forms	**X**	**X**	**X**	**X**	**X**	**X**

**X**, scheduled protocol-defined activity or assessment.

**Table 2 mps-09-00134-t002:** Conservative endpoint-specific design-sensitivity benchmarks for the fixed 9:1 randomized design.

Population	Primary Outcome	Assumed Control Risk	Detectable RESET Risk	Absolute Reduction	Odds Ratio	Relative Reduction
Oncology	Prolonged index hospitalization	20.0%	12.4%	7.6 pp	0.57	38%
Oncology	30-day readmission	12.0%	6.2%	5.8 pp	0.49	48%
Oncology	Postoperative complications	30.0%	21.0%	9.0 pp	0.62	30%
Non-oncology	Prolonged index hospitalization	15.0%	6.7%	8.3 pp	0.41	55%
Non-oncology	30-day readmission	10.0%	3.5%	6.5 pp	0.33	65%
Non-oncology	Postoperative complications	25.0%	14.2%	10.8 pp	0.50	43%

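### The readmission window runs 30 days from discharge, but the only interview scheduled in both arms is timed from surgery and usually falls before that window closes

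*Protocol article*

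**What the plan says.** Section 5 (Outcome Measures) starts the readmission clock at discharge and counts other hospitals: "Readmission is defined as an unplanned admission to the same or another hospital within 30 days after discharge from the index hospitalization". Section 5.1 names three sources: "Readmissions will be identified using electronic health records, hospital information systems, and participant follow-up interviews".

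The follow-up visit under section 4.5.4 is timed from a different event: "A follow-up interview will be conducted at day 30 ± 5 after surgery". It need not be in person: "The follow-up may be conducted by telephone or on site at the study center". The last column of Table 1 is "Final Visit 30-Day Post-Surgery Follow-Up", and no column refers to 30 days after discharge.

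Section 4.4 describes further contacts after discharge: "After discharge, transitional care includes scheduled follow-up contacts, reinforcement of discharge recommendations, and monitoring for complications and rehospitalization". No dates are given for them. Section 4.2 states that both arms follow the assessment schedule but that only the intervention arm receives the coordinated pathway, to which these contacts belong.

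The period of Module IV, which holds transitional care and the monitoring of rehospitalizations, is stated in two ways. The section 4.5.4 heading and Table 1 give 30 days after surgery. The Discussion describes the pathway as "spanning the preoperative, inpatient, and 30-day post-discharge periods".

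**The concern.** The outcome and the follow-up run on different clocks. Any participant discharged some days after surgery reaches the interview with part of the readmission window still to come, and the longer the stay, the larger that part.

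Of the three named sources, the interview is the one that plainly can reveal an admission to a hospital outside the two study centers. A late readmission of that kind is found only if the records reach it or someone asks again.

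Capture may also differ by arm, for two reasons. RESET participants have additional contacts that monitor for rehospitalization. RESET also aims to shorten the stay, which leaves more of its window covered at a surgery-anchored interview. Both would find proportionally more readmissions in RESET than in control.

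Readmission is one of three primary outcomes and supplies two of the six confirmatory tests. Analysis cannot recover events that were never ascertained, so the timing has to be settled in the follow-up schedule.

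**Working it through.** **1. Window against interview.** Let D be the postoperative day of discharge and V the postoperative day of the interview (25 to 35). The window closes on day D+30, so the days still open at the interview are max(0, D + 30 − V).

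| D | V = 25 | V = 30 | V = 35 |
|---|---|---|---|
| 1 | 6 | 1 | 0 |
| 3 | 8 | 3 | 0 |
| 5 | 10 | 5 | 0 |
| 7 | 12 | 7 | 2 |
| 10 | 15 | 10 | 5 |
| 14 | 19 | 14 | 9 |

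At the nominal day 30 the window is open for every D ≥ 1. At the latest permitted day, 35, it is open for every D > 5. An interview at discharge +30 would fall on day 37 for D = 7 and day 44 for D = 14, both outside the permitted range.

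**2. The plan's own figure.** Table 2, oncology readmission: control 12.0%, RESET 6.2% (6.21% before rounding), n = 570 and 5170, two-sided α = 0.01/6 = 0.00167, z = 3.144. Normal approximation with pooled null variance:

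- pooled risk = (570 × 0.12 + 5170 × 0.0621)/5740 = 0.0678
- SE under the null = 0.01110; SE under the alternative = 0.01402
- power = Φ[(0.0579 − 3.144 × 0.01110)/0.01402] = Φ(1.64) = 95%

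The stated 95% is reproduced.

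**3. Effect of the timing gap on power.** The documents give neither the length-of-stay distribution nor the share of readmissions known only from interview. Assumptions: a share e of 20% or 40% is known only from interview, the hazard is uniform over the 30 days, and the interview is on day 30. The captured fraction is (1 − e) + e × (30 − D)/30. It is applied to both arms of the Table 2 effect.

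| e | D control / RESET | Captured, control / RESET | Observed risk, control / RESET | Power |
|---|---|---|---|---|
| 20% | 9 / 7 | 0.940 / 0.953 | 11.3% / 5.9% | 92% |
| 40% | 9 / 7 | 0.880 / 0.907 | 10.6% / 5.6% | 89% |
| 40% | 12 / 9 | 0.840 / 0.880 | 10.1% / 5.5% | 85% |

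Relative to RESET, control capture is lower by 1.4% (1 − 0.940/0.953), 2.9% and 4.5%.

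With no true effect (12% in both arms), the same fractions give 11.3% vs 11.4%, 10.6% vs 10.9% and 10.1% vs 10.6%. RESET then looks slightly worse, by about 0.2 to 0.5 percentage points.

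**4. Effect of unequal contacts.** The model in step 3 ignores the additional RESET contacts. As a separate and harsher illustration, suppose RESET is fully captured and controls are under-captured:

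- by 5%: control 0.95 × 12% = 11.4% against 6.21%, power 89%
- by 10%: control 0.90 × 12% = 10.8% against 6.21%, power 80%

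The 10% case is more than twice the largest differential in step 3, so it needs the unequal contacts, and not only the difference in stay, to be plausible.

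**The case against.** The strongest reply is that interviews are only one source. Sections 5.1 and 5.6 both name electronic health records and hospital information systems. No cut-off at postoperative day 30 is stated for them, and the final analysis follows completed follow-up and database lock. A readmission to a study hospital on day 29 after discharge can be found whatever the interview date. The article is also a condensed account, and the full protocol may say how far the records reach. This stands, and it confines the concern to late readmissions that the records miss. It does not remove the concern, because other hospitals are part of the endpoint and the article does not say that the records cover them or are read after the window closes.

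A reader might infer that under-counting is established, or that the unasked days are entered as no readmission. The documents support neither. Section 5.6 leaves missing primary-outcome data to an approach that depends on extent, pattern and mechanism, and the article states no rule for an unfinished window.

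A reader might also object to a complication interview as early as day 25. That does not follow in the same way: complications are counted to day 30 after surgery, graded from the inpatient stay onward and also sought in records, and a visit tolerance does not shorten the outcome window.

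Finally, the bias described runs against RESET and would not manufacture a benefit. That limits the harm to a missed or shrunken effect, or an apparent disadvantage.

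**Conclusion.** The mismatch of anchors is in the current text and should be corrected. The one interview common to both arms covers the full readmission window only for participants discharged by postoperative day 5, and at D = 5 only if the visit falls on day 35.

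What is exposed is late readmission that records do not reach, chiefly to other hospitals, with capture probably better in RESET. The size is unknown. Under the assumptions in the working, power for the Table 2 oncology readmission effect is about 92-85% instead of 95%. The 89% and 80% figures require under-capture confined to controls, and they should not be read as the effect of the timing gap alone.

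How many participants are affected depends on lengths of stay and actual visit days, which the article does not give; the share would be smaller if visits clustered near day 35 after short stays. The two descriptions of Module IV's period are a lesser inconsistency that must be reconciled.

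**What to change.** - Ascertain readmission in both arms by the same scripted telephone contact and the same record extraction, at or after discharge +30 days. One way is to move the telephone follow-up to the later of surgery +30 and discharge +30.
- For the primary analysis, count only readmissions from sources applied to both arms, so that the RESET-only contacts do not add events.
- Treat participants not followed to discharge +30 as incompletely observed, and handle them under the missing-data plan.
- Reconcile the period of Module IV between the section 4.5.4 heading, Table 1 and the Discussion.

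The cost is a short amendment and a later or additional brief call for some participants. Telephone follow-up is already permitted, no new procedure is needed, and neither the sample size nor the endpoint definition changes. Recruitment is under way, so an early change limits the number of participants followed under the present schedule.

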### 5.1. Primary Endpoints

Participants with prolonged index hospitalization.

The outcome will be reported as the number and percentage of participants whose index hospitalization lasts at least 14 calendar days. The number of days beyond day 14 and the number of consecutive clinically unjustified Red days at the end of hospitalization will also be recorded.

2.Participants with an unplanned hospital readmission within 30 days after index hospital discharge.

Readmissions will be identified using electronic health records, hospital information systems, and participant follow-up interviews. The outcome will be reported as the number and percentage of participants with at least one unplanned readmission within 30 days after discharge.

Prolonged hospitalization and readmission will be compared between the RESET and standard-care arms. Additional analyses will describe the duration and reasons for prolonged hospitalization, time to readmission, causes of readmission, associated treatment, impact on the participant’s condition, and related costs.

3.Participants with at least one postoperative complication within 30 days after surgery.

Postoperative complications will be identified and graded using the Clavien–Dindo classification. The outcome will be reported as the number and percentage of participants with at least one Clavien–Dindo grade I-V complication within 30 days after surgery. For participants with multiple complications, the highest grade observed during this period will additionally be recorded.

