### 4.2. Exclusion Criteria

-Cancer diagnosis.

Up to 12,800 potentially eligible patients will be approached and screened. At the stage of offering participation, approximately 25–35% of eligible patients are expected to decline; a 30% non-participation rate is assumed for planning purposes. Individuals who decline will not undergo study procedures, although routinely available clinical outcomes may be used in prespecified exploratory comparisons where permitted. Approximately 8960 participants are therefore expected to provide consent and be randomized. Randomized participants are allocated to the RESET intervention (90%) or standard-care control arm (10%). Both randomized arms undergo the protocol-defined assessment schedule; only the intervention arm receives the coordinated RESET pathway.

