#### 4.2.2. Blinding

Because RESET is an individualized multidisciplinary care pathway, complete blinding is not feasible. In accordance with the approved study design and trial registration, participants are informed about study participation but are not explicitly told whether they have been allocated to the individualized RESET pathway or to standard perioperative care. Both groups undergo the same protocol-defined assessments, questionnaires, and activity monitoring. Some participants may nevertheless infer their allocation from the nature or intensity of care received; participant masking therefore refers to non-disclosure of randomized allocation rather than assurance that allocation cannot be recognized. Personnel delivering RESET are necessarily aware of allocation. Surgeons and other inpatient clinicians are not routinely informed of study allocation for research purposes, although information required for safe clinical care is never withheld. Outcome assessors and data analysts remain unaware of allocation whenever feasible. Allocation data are kept separate from outcome data, and the three primary outcomes are objective clinical endpoints.

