
Additionally, the RESET tool includes the following:Stochastic Organizational Support Network Planning: This is a model that reduces patient waiting times for specialist visits and improves resource allocation by optimizing niche specialist service availability;The Enhanced Recovery Protocol: This protocol focuses on maintaining nutrition, promoting early mobilization, and effective pain management [35,36,37];The Transitional Care Program: This program provides continuous monitoring and support after discharge to prevent rehospitalization, ensure follow-up care, and manage potential risks before complications arise [38].

Moreover, the SAFER Patient Flow Bundle [39] will be implemented to shorten patient stays and enhance the efficiency and safety of patient flow. The SAFER bundle is a practical strategy designed to minimize delays for adult patients in inpatient units. This practical tool combines five core best practices. Applying all five elements simultaneously is crucial for maximizing the overall benefits. When applied consistently, the SAFER bundle shortens patient stays and enhances the efficiency and safety of patient flow. The SAFER Patient Flow Bundle consists of the following:S (Senior Review): Every patient should receive a review by a senior clinician before midday. This clinician must have the authority to make care management and discharge decisions.A (All Patients): Each patient should be given an expected discharge date and clinical criteria for discharge, assuming an optimal recovery path with no unnecessary delays.F (Flow): Patient flow should begin promptly, transferring patients from assessment units to inpatient wards as early as possible.E (Early Discharge): The goal is for 33% of patients to be discharged from inpatient wards before noon.R (Review): A structured, multidisciplinary team assessment is required for patients with prolonged stays (over 7 days), with a focus on a “home first” approach.

Each of these elements is integral to achieving smoother patient transitions and optimizing hospital resources.

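### The any-grade day-30 complication endpoint does not say whether events known only through RESET's extra post-discharge contacts count, so minor events may be detected more often in that arm

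*Protocol article*

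**What the plan says.** **Endpoint.** Section 5.1 of the protocol article defines the outcome as the number and percentage of "participants with at least one Clavien–Dindo grade I-V complication within 30 days after surgery". There is no severity floor. The highest grade per participant is also recorded.

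**Follow-up common to both arms.** Section 4.2: "Both randomized arms undergo the protocol-defined assessment schedule; only the intervention arm receives the coordinated RESET pathway". Section 4.2.2: "Both groups undergo the same protocol-defined assessments, questionnaires, and activity monitoring". The day 30 ± 5 visit (section 4.5.4) is an interview meant to "document the postoperative course, and repeat applicable scales". Its mode is flexible: "The follow-up may be conducted by telephone or on site at the study center".

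**What RESET adds.** Section 4.4: "After discharge, transitional care includes scheduled follow-up contacts, reinforcement of discharge recommendations, and monitoring for complications and rehospitalization". Section 4.3 says of the Transitional Care Program: "This program provides continuous monitoring and support after discharge to prevent rehospitalization, ensure follow-up care, and manage potential risks before complications arise". Sections 4.3 and 4.4 also give RESET participants a coordinator and an app through which they can report needs and ask for support.

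**Sources.** Section 5.1 names sources for readmission but none for complications. Section 5.6 gives sources for all primary outcomes together: electronic records, hospital systems and scheduled follow-up. The list is open-ended and not split by arm.

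**Blinding.** Section 4.2.2 keeps outcome assessors unaware of allocation when feasible, acknowledges that RESET personnel know it, and states that "the three primary outcomes are objective clinical endpoints". Section 5 also describes the three outcomes as objectively defined.

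**The concern.** Whether a grade I event enters the data depends partly on how often someone asks. A mild problem at home may never reach a hospital record, and a participant may not mention it weeks later at a single interview. The intervention itself contains contacts that ask about complications, and complications are a primary endpoint. If those contacts feed the endpoint, the two arms are not measured with the same instrument.

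Extra detection in RESET raises its recorded rate. A true reduction is then diluted, and with no true effect RESET could appear to cause complications. Two of the six confirmatory tests, one per population, are exposed.

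Recruitment began on 16 February 2026 (section 7). If the source of an event is not captured when it is recorded, an analysis plan finalized before database lock may be unable to recover it.

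**Working it through.** **1. Do the sections settle which events count?** No.
- Section 5.1 fixes grade and window but gives no source for this outcome.
- Section 5.6 lists scheduled follow-up. This can mean the day-30 visit alone, or also the follow-up contacts that section 4.4 describes as scheduled. Both readings fit.
- Table 1 has separate rows for the RESET intervention and the Transitional Care Program. It also marks physical exam, medical scales and visit forms in the Module IV column without separating the arms.
- No section excludes events known only from RESET contacts.

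**2. Reproduce Table 2.** Inputs (sections 5.4, Table 2 and its note): two-sided α = 0.01/6 = 0.00167, so z = 3.144. Oncology has 570 control and 5170 RESET participants, with 30.0% against 21.0%. Non-oncology has 320 and 2900, with 25.0% against 14.2%.

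Power = Φ{[(pC − pR) − z·SE0]/SE1}, where SE0 = √[p̄(1−p̄)(1/nC + 1/nR)], p̄ is the pooled risk, and SE1 = √[pC(1−pC)/nC + pR(1−pR)/nR].

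Solving for 95% power gives pR = 20.97% and 14.21%, which round to the Table 2 entries.
- Oncology: p̄ = 0.2187, SE0 = 0.01824, SE1 = 0.02001. (0.0903 − 3.144 × 0.01824)/0.02001 = 1.65, power 95.0%.
- Non-oncology: p̄ = 0.1528, SE0 = 0.02120, SE1 = 0.02506. (0.1079 − 3.144 × 0.02120)/0.02506 = 1.65, power 95.0%.

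The plan's figures reproduce. They assume equal ascertainment in both arms.

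**3. Inflate the recorded RESET risk.** The documents give no detection rates, so the inflation f is an assumption. Replace pR by pR(1 + f).

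| f on total RESET rate | Oncology, α 0.00167 | Non-oncology, α 0.00167 | Oncology, α 0.01 | Non-oncology, α 0.01 |
|---|---|---|---|---|
| 0 | 95.0% | 95.0% | 98.5% | 98.3% |
| 2% | 92.2% | 93.5% | 97.4% | 97.7% |
| 3% | 90.4% | 92.6% | 96.6% | 97.3% |
| 10% | 69.6% | 83.9% | 85.2% | 93.1% |

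Example, oncology at 10%: pR = 0.2307, SE0 = 0.01878, SE1 = 0.02007. (0.0693 − 3.144 × 0.01878)/0.02007 = 0.51, power 70%.

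**4. Which f is plausible?** Extra contacts after discharge change only participants with no earlier counted event. If 20–30% of counted RESET participants have post-discharge events only, and these rise by 10%, then f = 0.20 × 10% = 2% to 0.30 × 10% = 3%. For f = 10%, the post-discharge-only cases would have to rise by 10/0.30 = 33% to 10/0.20 = 50%. All of these shares are assumptions.

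**5. No true effect, oncology, 30% true risk in both arms.** With f = 10%, the recorded RESET risk is 33%, OR = (0.33/0.67)/(0.30/0.70) = 1.15, and the same formula gives a 12.5% chance of nominal p < 0.01 against RESET. With f = 3% the chance is 1.6%. Without bias it is 0.5%.

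**The case against.** The strongest reply is that the arms already share the instruments that matter. Both have the day-30 interview, the same record sources and the same activity monitoring. Assessors are masked when feasible, surgeons and ward clinicians are not routinely told the allocation, and allocation data are kept apart from outcome data. Most events in hospital, and those leading to readmission, would be found either way. Sensitivity analyses belong in the analysis plan, and choosing an any-grade endpoint is a legitimate preference.

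Much of this stands and rules out stronger readings that a reader might infer:
- That only RESET participants are followed for complications after discharge. The shared interview contradicts this; RESET has additional contacts, not the only ones.
- That detection does differ by arm. No section states or quantifies this. It is a risk.
- That wristband review is one-sided. Sections 4.2.2 and 4.4 apply activity monitoring to both arms.
- That RESET is watched more closely for complications in hospital. The continuous inpatient monitoring in section 4.4 concerns adherence to recovery principles and standard care.
- That RESET staff grade events leniently and create a false benefit. No section assigns grading to them.
- That a 10% inflation is the expected size. It inflates in-hospital events too, which the extra contacts cannot affect.

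The reply does not answer the remaining point: the article fixes an any-grade endpoint and an arm-specific monitoring schedule without saying whether the second feeds the first. The limitations in section 6 do not mention it.

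**Conclusion.** The concern holds as an unresolved ascertainment rule that should be settled while recruitment is under way. The likely direction is against RESET. The size is unknown: at the first Holm step, a small inflation (2–3%) costs about 3–5 percentage points of power in oncology and 1–2 in non-oncology, while 10% costs about 25 and 11. Section 5.4 describes that step as a conservative benchmark. At α = 0.01, 10% inflation still leaves 85% and 93%. These figures rest on the Table 2 risks, the planned arm sizes, the pooled normal approximation, and inflation levels that are assumptions.

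Separately, the description of this outcome as objective is too strong for low-grade events. It suits length of stay, and largely readmission, better.

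**What to change.** 1. State that the primary complication endpoint is ascertained from sources applied identically to both arms: hospital records, including readmissions, and the same structured day-30 interview.
2. Add a field for the source of each event to the form now, while recruitment continues.
3. Report events known only from RESET contacts separately, with a prespecified sensitivity analysis that includes them.
4. Grade from an extract masked to arm, and to RESET contacts, where feasible.
5. Prespecify sensitivity analyses at grade II or higher and grade III or higher, using the highest grade already recorded.
6. Clarify which Module IV entries in Table 1 apply to both arms, and stop calling this outcome objective without qualification.

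The cost is wording, one form field and some work on the grading extract; no visit is added and care does not change. Slightly fewer events would be counted. Some true RESET events that leave no hospital record and are not reported at the day-30 interview would drop out of the primary count. That exclusion is one-sided and could favour RESET, which is why the inclusive analysis in item 3 is needed.
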